### 2.3. Setting and participating centers

Four Italian sleep centers participate in DREAMER:

Oasi Research Institute-IRCCS, Troina, Italy, serving as coordinating and recruiting center.University Hospital of Cagliari, Sleep Disorders Research Center, serving as recruiting center and neurophysiology site.IRCCS Istituto delle Scienze Neurologiche di Bologna, serving as recruiting center and brainstem neurophysiology site.IRCCS Ospedale San Raffaele Turro, Milan, serving as recruiting center and brainstem neurophysiology site.

All participating centers have established expertise in sleep medicine, RBD assessment, vPSG acquisition and scoring, and clinical neurophysiology. The multicenter structure is intended to increase recruitment feasibility, improve generalizability across sleep-clinic populations, and enable harmonized data collection across distinct operational environments.

### 2.4. Study population, inclusion and exclusion criteria

Participants will be recruited among adults undergoing full-night laboratory vPSG for clinical indications at participating centers. The target population is intentionally pragmatic: it reflects real-world sleep-center populations in which incidental RSWA may be detected and future risk stratification may become clinically relevant.

Participants must meet all of the following criteria:

Age ≥ 40 years at baseline.Ability to understand study procedures and provide written informed consent.Undergoing full-night laboratory vPSG with video recording.Availability of chin electromyographic signal of sufficient technical quality for RAI computation.At least 5 minutes of artifact-free REM sleep.No prior clinical diagnosis of RBD.

Collateral history from a bed partner, roommate, or other reliable informant will be collected whenever available to improve ascertainment of dream-enactment behavior. This is particularly important because the distinction between iRSWA and iRBD may be influenced by the availability of an observer or co-sleeper, potentially leading to under-recognition of dream-enactment behavior [12].

Participants will be excluded if any of the following are present:

Prior diagnosis of RBD.Severe neurological, psychiatric, cognitive, or general medical condition that prevents valid participation or understanding of study procedures.vPSG recordings with major artifacts affecting the chin EMG signal during REM sleep.Less than 5 minutes of artifact-free REM sleep.Withdrawal of consent.

The protocol will record medications known to influence REM sleep muscle tone, particularly antidepressants, as well as comorbid sleep disorders and neurological conditions. These factors will not automatically exclude participation unless specified by the final protocol or judged to preclude valid classification, but they will be incorporated into sensitivity analyses.

### 2.5. Baseline assessment

At baseline, all participants will undergo standardized clinical assessment, including demographic characteristics, medical history, neurological history, psychiatric history, cognitive status when clinically indicated, sleep history, history of dream-enactment behavior, sleep-related injuries, parasomnia symptoms, and medication exposure. Particular attention will be paid to antidepressants, dopaminergic medications, benzodiazepines, melatonin, antipsychotics, and other drugs that may influence REM sleep physiology or motor behavior during sleep.

Sleep history will include symptoms of insomnia, excessive daytime sleepiness, obstructive sleep apnea, restless legs syndrome, periodic limb movements, narcolepsy-related symptoms when relevant, and other parasomnias. Standardized RBD screening questionnaires may be used as supportive tools but will not replace clinical and vPSG-based classification.

All participants will undergo full-night laboratory vPSG according to the procedures routinely used in participating centers and harmonized through the DREAMER protocol. Recordings will include electroencephalography, electrooculography, submental electromyography, electrocardiography, respiratory channels, limb electromyography, oxygen saturation, body position, and synchronized video. Sleep staging and respiratory and movement events will be scored according to the current standards adopted by each center and harmonized for the variables included in the DREAMER eCRF.

The key classification variable is RSWA quantified by the RAI. The RAI is an automated measure derived from submental EMG amplitude during REM sleep and has been proposed as part of a practical approach to improve diagnostic accuracy and accessibility in RBD assessment [13]. Values range from 0, indicating complete absence of EMG atonia, to 1, indicating stable EMG atonia [14,15]. The DREAMER protocol adopts the established three-level RAI classification: > 0.9 normal, 0.8–0.9 mildly abnormal, and <0.8 definitely abnormal [14–16]. Participants with RAI < 0.85 and no clinical RBD will be classified as having isolated RSWA, while sensitivity analyses will explore alternative RAI thresholds, including <0.8.

The RAI algorithm will be applied blind to clinical classification whenever feasible. Because the RAI is computed automatically, no manual adjustment of the algorithmic output will be permitted. Technical adequacy checks will focus on chin EMG quality, artifact burden, and the minimum REM sleep duration required for valid computation.

### 2.6. Ancillary neurophysiological and biomarker assessments

DREAMER incorporates ancillary assessments to generate mechanistic and trial-readiness information beyond vPSG [17].

The coordinating center will perform transcranial magnetic stimulation (TMS) in participants with isolated RSWA and in an appropriate comparison group without RSWA. TMS will assess cortical excitability and inhibitory/facilitatory intracortical mechanisms. The aim is to determine whether isolated RSWA is associated with early cortical neurophysiological changes analogous to those described in RBD or early synucleinopathy [18].

The Cagliari center will perform cervical, masseter, and ocular vestibular-evoked myogenic potentials when feasible. These measures provide information on brainstem pathways that may be relevant to REM atonia regulation and early RBD-related neurophysiology [19]. Startle response assessment may also be included according to the final harmonized protocol.

The Bologna and San Raffaele centers will perform brainstem auditory evoked potentials in selected participants with isolated RSWA and matched comparators without RSWA. These measures will complement other neurophysiological assessments of brainstem function.

Blood samples will be obtained whenever possible, with priority given to participants with isolated RSWA. Samples will be processed and stored for future proteomic, metabolomic, and glycomic analyses. The purpose is to determine whether isolated RSWA is associated with peripheral molecular signatures overlapping with those previously described in isolated RBD [20,21].

Brain magnetic resonance imaging, computed tomography, dopamine transporter imaging, or other investigations will not be mandated by the protocol, but may be performed when clinically indicated as part of routine diagnostic work-up. Results will be recorded in the eCRF when available.

### 2.7. Outcomes

The main outcomes of the 24-month cohort-construction phase are:

Number of participants screened, eligible, enrolled, and classifiable by RAI.Frequency of isolated RSWA among enrolled participants.Completeness and quality of vPSG, clinical, neurophysiological, and biosample data.Feasibility of harmonized multicenter eCRF-based data capture.Recruitment rate and retention readiness for long-term follow-up.

The primary long-term clinical outcome is incident RBD, defined by development of clinical dream-enactment behavior with vPSG evidence of RSWA according to accepted diagnostic criteria.

Secondary long-term outcomes include:

Change in RAI over time, when repeat vPSG is available.Development of subthreshold dream-enactment behavior or increased RBD questionnaire scores.Diagnosis of Parkinson disease, dementia with Lewy bodies, multiple system atrophy, or other neurodegenerative disorders.Association between baseline RAI and neurophysiological markers.Association between baseline RAI and blood-based proteomic/metabolomic/glycomic signatures.Attrition, loss to follow-up, and feasibility of repeated annual assessment.

The procedures used to identify and confirm these outcomes during follow-up are described below.

### 2.8. Follow-up procedures and phenoconversion ascertainment

Participants classified as having isolated RSWA and a comparator group without isolated RSWA will be invited to participate in longitudinal follow-up. Follow-up will be performed at least annually by in-person visit, telephone interview, video consultation, or review of clinical records, according to participant availability and local center procedures. The follow-up strategy is designed to detect two clinically relevant forms of phenoconversion: conversion to clinically manifest RBD and conversion to a neurodegenerative disorder within the alpha-synucleinopathy spectrum, in line with longitudinal evidence from isolated RBD cohorts and biomarker-based models of conversion risk [2,3].

At each follow-up contact, participants will be asked about the occurrence of new dream-enactment behavior, vocalizations or complex motor behaviors during sleep, sleep-related injuries, falls from bed, violent or disruptive sleep behaviors, and changes in sleep quality. Whenever possible, information will also be obtained from a bed partner, caregiver, roommate, or other reliable informant. Follow-up assessments will also record changes in medication exposure, especially antidepressants, benzodiazepines, melatonin, dopaminergic medications, antipsychotics, and other drugs potentially influencing REM sleep muscle tone or parasomnia expression. New diagnoses of sleep disorders, neurological disorders, psychiatric disorders, and relevant systemic illnesses will be recorded.

Incident RBD will be suspected when new recurrent dream-enactment behavior or other clinically relevant REM sleep-related motor behaviors are reported by the participant or an informant. In these cases, participants will be invited to undergo repeat full-night laboratory video-polysomnography, including chin electromyography and video documentation, whenever feasible. Incident RBD will be defined by the emergence of clinical dream-enactment behavior together with polysomnographic evidence of RSWA, according to accepted diagnostic criteria [1,22]. For each suspected or confirmed case, the date of first reported symptoms, date of clinical recognition, and date of polysomnographic confirmation will be recorded separately.

Phenoconversion to neurodegenerative disease will be assessed through annual clinical history, neurological review, and documentation of any new diagnosis of Parkinson disease, dementia with Lewy bodies, multiple system atrophy, or other relevant neurodegenerative disorders, using established diagnostic frameworks where applicable [23–25]. Follow-up data collection will include symptoms or signs suggestive of parkinsonism, cognitive decline, visual hallucinations, fluctuating cognition, autonomic dysfunction, gait impairment, olfactory impairment, and other non-motor manifestations potentially relevant to prodromal synucleinopathy, consistent with research criteria and updates for prodromal Parkinson disease [26,27]. This approach is also supported by longitudinal application of prodromal Parkinson disease criteria in RBD cohorts [28].

When clinically indicated, participants will be referred for neurological evaluation and additional investigations according to local clinical practice, including neuropsychological testing, autonomic assessment, brain imaging, dopamine transporter imaging, or other biomarker investigations. These tests are not mandated by the protocol but will be recorded when available.

All suspected phenoconversion events will be reviewed by the recruiting center and, when necessary, discussed centrally by the study investigators. Outcome adjudication will use predefined criteria and will distinguish between no conversion, possible RBD, confirmed RBD, possible neurodegenerative phenoconversion, and confirmed neurodegenerative diagnosis. For longitudinal analyses, the event date will be defined as the earliest reliable date of symptom onset when available; otherwise, the date of clinical diagnosis or polysomnographic confirmation will be used. Participants who cannot be contacted will be classified as lost to follow-up after repeated contact attempts, and the date of last available assessment will be recorded.

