**Baseline**	Medication and comorbidity assessment	X	X
**Baseline**	Full-night laboratory vPSG	X	X
**Baseline**	RAI computation	X	X
**Baseline**	RBD symptom/questionnaire assessment	X	X
**Baseline**	TMS	As feasible	Priority
**Baseline**	VEMPs/startle response	As feasible	Priority
**Baseline**	BAEPs	As feasible	Priority
**Baseline**	Blood sampling for biobank	As feasible	Priority
**Follow-up**	Annual assessment for dream-enactment behavior	Planned	X
**Follow-up**	Repeat vPSG	If clinically indicated or protocol-defined	X
**Follow-up**	Neurodegenerative outcome ascertainment	Planned	X

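### Section 2.8 lets record review alone stand as the annual follow-up, so the text permits chart-only time after the last direct contact to count as free of RBD

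*Protocol article*

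**What the plan says.** All references are to the protocol article.

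- **Permitted modes (section 2.8).** "Follow-up will be performed at least annually by in-person visit, telephone interview, video consultation, or review of clinical records". The choice is made "according to participant availability and local center procedures". No minimum frequency of direct contact is set, and record review is not confined to neurodegenerative diagnoses. The sentence that follows says this strategy is meant to detect conversion to RBD as well as to a synucleinopathy.
- **How dream enactment is elicited (section 2.8).** "At each follow-up contact, participants will be asked about the occurrence of new dream-enactment behavior". Incident RBD is suspected when new behaviors "are reported by the participant or an informant".
- **Schedule (Table 2).** The row "Annual assessment for dream-enactment behavior" carries an X for the isolated RSWA subgroup and only the word Planned for all enrolled participants.
- **Outcome (section 2.7).** "The primary long-term clinical outcome is incident RBD, defined by development of clinical dream-enactment behavior with vPSG evidence of RSWA".
- **Dates (section 2.8).** For events, "the event date will be defined as the earliest reliable date of symptom onset when available". For participants who cannot be contacted and are classed as lost, "the date of last available assessment will be recorded".
- **Analysis (section 2.11).** Kaplan-Meier and Cox models for incident RBD, the latter adjusted for center among other covariates.

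**The concern.** The outcome starts with someone describing a behavior during sleep. A record review puts the question to nobody, and a chart that is silent on dream enactment is not a negative answer. A center could therefore meet the follow-up requirement every year and never carry out the assessment on which the primary long-term outcome depends.

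If the last assessment on file is a chart review, and that date serves as the end of RBD-free time, the person-time since the last real inquiry adds to the denominator with little chance of adding an event. Incidence would come out too low. If comparators were followed by chart more often than participants with isolated RSWA, their rate would be lowered more and the hazard ratio would be inflated, in the direction of the study hypothesis. The different markings in Table 2 make such a difference conceivable. Section 2.9 intends the relative-risk estimates for planning future prevention or neuroprotection trials.

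**Working it through.** **The text, set side by side.** The sentence on modes makes record review sufficient for a year of follow-up. The sentence on questioning and the trigger for suspected RBD both need a person to answer. The first can be satisfied without the other two. The date of last available assessment is not restricted by mode, so it can be a chart date.

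**Which chart-only time matters.** Events are dated to symptom onset when that is available. Onset during a chart-only year can therefore be recovered at a later interview. What remains is chart-only time after the last direct contact.

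**Scale.** The plan gives no figure on this point, so there is none to reproduce. From the documents: n = 85 with isolated RSWA (section 2.9) and 5 years of follow-up (section 2.12). Assumed, because the documents do not give them:

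- constant RBD hazard λ of 0.02 to 0.08 per year;
- a share f of 10% to 50% followed by records only in the last m = 1 to 3 years;
- no detection from records (the worst case).

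With T = 5 − m:

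- true events = n(1 − e^(−5λ))
- missed events = n·f·(e^(−Tλ) − e^(−5λ))
- unassessed person-years = missed events / λ
- person-years if chart-only time is credited = n(1 − e^(−5λ))/λ + n·f·e^(−Tλ)·[m − (1 − e^(−mλ))/λ]

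Worked case, λ = 0.05, f = 0.25, m = 2, T = 3:

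- true events = 85 × (1 − 0.7788) = 18.8, over 18.8/0.05 = 376.0 person-years
- missed = 85 × 0.25 × (0.8607 − 0.7788) = 1.7, leaving 17.1
- credited person-years = 376.0 + 85 × 0.25 × 0.8607 × (2 − 1.9033) = 377.8
- rate = 17.06/377.8 = 0.045, which is 0.903 of the true rate
- censored at the last direct contact: 17.06 events over 376.0 − 34.8 = 341.2 person-years = 0.050, the true rate

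| λ = 0.05 | Events seen (true 18.8) | Unassessed person-years | Rate if chart time is credited | Fraction of truth |
|---|---|---|---|---|
| f = 10%, m = 1 | 18.5 | 6.8 | 0.049 | 0.982 |
| f = 25%, m = 2 | 17.1 | 34.8 | 0.045 | 0.903 |
| f = 50%, m = 3 | 13.4 | 107.1 | 0.035 | 0.700 |

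Over λ = 0.02 to 0.08 the fraction runs from 0.982 to 0.700, so incidence is understated by about 2% to 30%. Unassessed time runs from about 6 to 119 person-years.

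**Rate ratio.** Assume a true ratio of 3.0 (0.05 against 0.05/3 per year).

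- Equal use in both groups (10% and 10%, or 50% and 50%): 3.0, and 3.02 at most.
- 10% in isolated RSWA against 30% in comparators, last 2 years: 3.0 × 0.961/0.881 = 3.27.
- 10% against 50%, last 3 years: 3.0 × 0.939/0.700 = 4.02.

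**The case against.** The best reply is that the passages can be read together. A record review is not a contact, Table 2 schedules an annual dream-enactment assessment, and so direct questioning is already required, with records filling gaps and serving the neurodegenerative outcomes. That reading is possible. But the sentence on modes offers the four as alternatives, with no floor on direct contact, and is followed by the statement that the strategy serves detection of RBD. A center following that sentence would not be deviating.

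Several counterpoints stand and limit the claim:

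- **Accrual is not stated.** A reader might infer that participants do gather event-free time in chart-only years. The article gives no censoring rule for RBD, and a condensed article may leave that to a fuller plan. The fault is in what the stated rule permits.
- **Non-responders are not kept as retained.** A reader might infer that someone who never answers but has a hospital record stays in the cohort and lowers reported attrition. Section 2.8 classes people who cannot be reached after repeated attempts as lost to follow-up. What survives is that the date recorded for them may come from a chart.
- **Center differences alone.** A reader might infer that different local habits bias the hazard ratio by themselves. The Cox model adjusts for center, and a loss common to both groups within a center largely cancels. A difference between the RSWA groups is needed.
- **Charts are insensitive, not blind.** Records can hold a volunteered report or an RBD diagnosis, so zero detection is an upper bound on the loss.
- **Modest purpose.** Section 2.9 calls the estimates preliminary. That lowers the stakes without removing the conflict.

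**Conclusion.** The point holds in a limited form. Section 2.8 lets record review alone satisfy the annual follow-up while its own trigger for incident RBD needs a participant or informant report, and the last-assessment date is not tied to direct contact. Chart-only time after the last direct contact may therefore count as RBD-free. Earlier chart-only years are largely recoverable through onset dating.

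The effect on incidence is a downward bias of unknown size, about 2% to 30% under the assumed hazards, shares, durations and zero chart detection. The hazard ratio is nearly unaffected if chart-only use is equal in the two groups. It moves, for example from 3.0 to about 3.3 or 4.0, only under an assumed imbalance that the documents neither state nor rule out. This is a cheap improvement, not a flaw that invalidates the design.

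**What to change.** In section 2.8:

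- State that record review may add a diagnosis or a date but does not count as the annual dream-enactment assessment.
- For incident RBD, censor each participant at the last visit, telephone or video contact at which the participant or an informant was asked the dream-enactment questions, with the same rule in both groups.
- Say how an RBD entry found only in records after that date is handled. Counting the event while dropping the surrounding time would bias the rate upward, so such cases fit a sensitivity analysis unless a later direct contact takes the history.
- Count records-only years as missed dream-enactment assessments.
- Keep record review valid for neurodegenerative diagnoses, with a separate censoring date.

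Add a contact-mode field to the eCRF and report mode by group.

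The cost is a few sentences and one data field, plus somewhat shorter RBD person-time and a less favourable completeness figure. In the worked case the loss is 34.8 of 376.0 person-years (9%), with no observed event given up. Section 2.12 places follow-up after recruitment, data validation and cohort constitution, so a change made before then touches no follow-up data. Contact mode is hard to reconstruct later if it was never recorded.

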### 2.10. Data management and quality assurance

A web-based eCRF will be developed by the coordinating center. The data architecture will include a relational database for storage, a secure web service for data management, and a client-side web application for authorized users. The system will support data entry, display, modification, and controlled deletion according to predefined user permissions.

Data will be pseudonymized before entry into the central database. Access will be role-based and password-protected. The system will be hosted on secure institutional infrastructure. Privacy, cybersecurity, and data-protection procedures will be supervised with involvement of data-protection and information-technology expertise at the coordinating institution.

A data dictionary will define all mandatory, optional, and derived variables. Harmonized fields will include demographic data, vPSG variables, RAI values, sleep-disorder diagnoses, RBD-related symptoms, neurological history, medication exposure, neurophysiological test results, biosample status, and follow-up outcomes.

Quality-control procedures will include:

Standard operating procedures for vPSG acquisition and RAI computation.Training meetings among centers before recruitment.Predefined rules for technical adequacy of chin EMG and REM sleep duration.Automated eCRF range checks and missing-data flags.Periodic cross-center data-quality reports.Central review of ambiguous classification cases.Documentation of protocol deviations.

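### Suspected phenoconversion events are reviewed by a recruiting center that very likely knows the baseline RSWA group, with conditional central discussion and no stated masking of outcome reviewers

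*Protocol article*

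**What the plan says.** **Who reviews.** Section 2.8 states: "All suspected phenoconversion events will be reviewed by the recruiting center and, when necessary, discussed centrally by the study investigators". It gives no trigger for the central step.

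**With what criteria.** The next sentence of Section 2.8 begins "Outcome adjudication will use predefined criteria and will distinguish between no conversion, possible RBD, confirmed RBD" and goes on to possible and confirmed neurodegenerative categories, five in all. For the longitudinal analyses, the event is dated from the earliest symptom onset considered reliable. Failing that, the date of diagnosis or of polysomnographic confirmation is used.

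**The outcome.** Section 2.7: "The primary long-term clinical outcome is incident RBD, defined by development of clinical dream-enactment behavior with vPSG evidence of RSWA". Section 2.8 describes the trigger: "Incident RBD will be suspected when new recurrent dream-enactment behavior or other clinically relevant REM sleep-related motor behaviors are reported". Such a report may come from the participant or from an informant. Repeat vPSG is then offered where feasible.

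**Masking.** The only masking statement is in Section 2.5 and concerns the exposure measurement: "The RAI algorithm will be applied blind to clinical classification whenever feasible". It is followed by "Because the RAI is computed automatically, no manual adjustment of the algorithmic output will be permitted". Section 2.10 lists, under quality control, "Central review of ambiguous classification cases", without masking.

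**The analysis.** Section 2.11 plans Kaplan-Meier curves and a Cox model of incident RBD on baseline isolated RSWA.

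**The concern.** The long-term question is whether isolated RSWA leads to RBD. If the person who decides whether a report counts as RBD knows that the participant has isolated RSWA, an unclear account may be read more readily as conversion than the same account from a comparator. The same applies to the choice of onset date and to soft neurological signs. Covariate adjustment in the Cox model does not correct outcome classification that depends on exposure, and neither do the sensitivity analyses listed in Section 2.11 (antidepressants, REM duration, sleep apnea, RAI threshold).

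What is at stake is the relative-risk estimate that Section 2.9 says will be used to plan later prevention or neuroprotection trials. With about 85 isolated-RSWA participants expected, a few events judged differently could move it. The 24-month cohort-construction outcomes in Section 2.7 are not affected.

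**Working it through.** The plan gives no figure for adjudication accuracy, so there is none to reproduce. The check sets the sections side by side.

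**1. Is this only something a condensed article leaves out?** Not entirely. Section 2.8 makes a positive choice: local review of every suspected event, with central discussion only where it is thought necessary. The absence of masking is silence, but the local-first structure is stated.

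**2. Will the recruiting center know the group?** No section says so; it is an inference from four facts.
- The recruiting centers perform the baseline vPSG (Sections 2.4 and 2.5).
- RAI classification and comparator selection come before follow-up begins (Section 2.12).
- Table 2 gives different follow-up entries by group. Repeat vPSG is marked outright for the isolated-RSWA subgroup but is conditional for all enrolled. Annual dream-enactment assessment and neurodegenerative ascertainment are marked for the subgroup but only planned for all enrolled. A center cannot run that schedule without knowing the group.
- Section 2.6 ranks participants by group for sampling: "Blood samples will be obtained whenever possible, with priority given to participants with isolated RSWA".

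Together these make knowledge of the group very likely.

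**3. Where does judgement remain after the safeguards?**

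| Element | Safeguard in the article | What is left to judgement |
|---|---|---|
| Dream-enactment behavior | Predefined criteria | Whether a reported behavior is recurrent and clinically relevant; informant only when available |
| RSWA on vPSG | Required for RBD under accepted diagnostic criteria | Little, once recorded; but repeat vPSG depends on feasibility |
| Possible versus confirmed RBD | Predefined criteria | Weighing the clinical part of the definition |
| Neurodegenerative categories | Established frameworks where applicable | Possible versus confirmed |
| Event date | Rule of precedence | Which reported onset is reliable |

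The vPSG requirement protects less in the exposed group than it first appears. Those participants were classified by RAI below 0.85 at baseline, so many may already meet the recording part of the definition. What must be newly established is then mainly the clinical part, where judgement is greatest.

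**4. Direction.** Let p be the true risk, taken as equal in both groups, and let Se and Sp be the sensitivity and specificity of classification in isolated RSWA (1) and comparators (0). The observed relative risk is

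[p·Se1 + (1 − p)(1 − Sp1)] / [p·Se0 + (1 − p)(1 − Sp0)].

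With Se1 = Se0 and Sp1 = Sp0 this equals 1. If knowledge of the group makes reviewers readier to accept events in isolated RSWA, Se1 rises, Sp1 falls, or both. The numerator then grows and the ratio exceeds 1. The documents give no value for p, Se or Sp in either group, so only the direction follows.

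**The case against.** **The safeguards are real.** Adjudication uses predefined criteria, confirmed RBD needs vPSG evidence, and a separate category exists for unconfirmed reports. This stands. It narrows the room for bias but does not close it, because criteria can still be applied differently by someone who knows the exposure.

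**Masking may be in the full protocol or an adjudication manual.** It may be. Any such text would have to be squared with the review structure that Section 2.8 states, so the article needs clarifying in either case.

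**Knowledge of the group is inferred.** True. Comparators also receive ancillary tests (Section 2.6), so testing alone does not reveal group. The group-specific schedule in Table 2 is the stronger ground.

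**The consequence is limited.** Section 2.9 calls the estimates preliminary and intends them for planning, and the Discussion already says that follow-up requires harmonized adjudication. This bounds the importance of the point but does not answer it, since an inflated estimate would pass into the trials planned from it.

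**Stronger readings that do not hold.** A reader might infer that the four centers apply different thresholds. Nothing in the article shows this, and shared predefined criteria point the other way. A reader might also put a size on the bias by assuming different confirmation rates in the two groups. That fails: confirmation requires RSWA on vPSG and the exposed group was selected for RSWA, so the rates would differ legitimately even under perfect masking. Finally, masking the RAI is not itself a fault; Section 2.5 also has technical adequacy checks that may need human judgement.

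**Conclusion.** The point holds in limited form. The article assigns review of every suspected event to a center that very likely knows the baseline RSWA group, leaves the central step conditional without a trigger, and states no masking of outcome reviewers. The comparison of incident RBD and of neurodegenerative outcomes by baseline RSWA is therefore open to differential classification and dating, tending to raise the hazard ratio for isolated RSWA. The size cannot be derived from the documents.

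The conclusion rests on two assumptions: that local reviewers know the group, and that no unseen document masks them. It should be corrected before follow-up events are adjudicated, because classifications already made with knowledge of the group cannot be masked afterwards without fresh review.

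**What to change.** In Section 2.8:

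- Send every suspected event to the existing central investigator discussion.
- Have each event classified and dated against the predefined criteria by an investigator from a center other than the one that recruited that participant. All four centers recruit (Section 2.3), so the rule has to be set participant by participant.
- Hide baseline RAI, RSWA group and ancillary results from that investigator through the role-based eCRF access already described in Section 2.10.
- Have the clinical and informant record judged, and that judgement recorded, before the repeat vPSG is opened. The recording shows current RSWA and may reveal the baseline group, so masking is only partial.
- Use this classification and date in the Cox analysis. Clinical care stays with the recruiting center.

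**Cost.** New wording in Section 2.8, an access setting in the eCRF, and some time from existing investigators for each suspected event; no added participant procedures. Recruitment is expected to close by 30 June 2026 and follow-up starts after that and after baseline validation (Section 2.12), so the rule can be in place first.

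**What it leaves open.** It does not correct unequal ascertainment, that is, differences between groups in who is suspected or who receives a repeat vPSG.
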